#### Development of the DENV specific genome-scale metabolic model (GEM)

We will first develop the DENV specific GEM by infecting the human monocyte derived macrophages (MDMs) with all four dengue serotypes (DENV-1 to DENV-4). Anonymized PBMCs are also collected from the healthy blood donors for in vitro infection experiments. MDMs will be infected and samples will be collected at 6 h, 12 h, 24 h, 36 h and 48 h post-infection. Transcriptomics, proteomics and metabolomics will be performed to develop the DENV GEM as described by us previously in SARS-CoV-2 [15]. Additionally, we will perform scRNA-seq, assess DNA methylation changes by bisulfite pyrosequencing, and utilize super-resolution microscopy to characterize the microenvironment during viral infection (Fig. 1).

**Fig. 1 Fig1:**
[figure not shown]
Ex vivo GEM and deep profiling of viral infection microenvironment

#### Personalized GEM to bridge and improve the ex-vivo cell-based DENV-GEM

To further improve a DENV GEM developed in an ex vivo assay, we will add the patient-based GEM both from bulk sequencing and scRNA-seq data to improve the predictability of the immunomodulator. We will use the personalized GEM developed recently to avoid heterogeneity by adding the viral biomass objective function (VBOF). We will provide feedback on the essential gene-metabolite knock-out (KO) module to the initial DENV-GEM to improve the identification of the immunomodulator [10].

#### Artificial intelligence (AI) models for DENV severity

The assessment of DENV severity using traditional methods has proven difficult due to many contributing factors, such as variation in symptoms, dynamic nature of dengue infection, and lack of specific biomarkers, amongst others [8]. Multiple machine-learning and deep-learning models, including logistic regression, random forests, XGBoost, support vector machines, multilayer perceptrons, and multimodal neural-network architectures, will be trained and systematically compared for DENV severity prediction. The models will integrate available clinical, laboratory, demographic, virological, and multi-omics data, using feature-selection and dimensionality-reduction approaches. Model interpretability will be assessed using explainable AI approaches, including SHapley Additive exPlanations (SHAP) and Local Interpretable Model-agnostic Explanations (LIME), to identify the variables and molecular features driving individual- and cohort-level predictions. Temporal and geographical robustness will be evaluated using time-split validation, external validation across sites, and leave-one-site-out cross-validation. Model performance will be assessed using AUROC, AUPRC, sensitivity, specificity, F1-score, calibration, and decision-curve analysis to identify clinically robust and generalizable models for DENV severity prediction.

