## Background

Dengue is a mosquito-borne viral infection with a wide clinical spectrum ranging from self-limiting febrile illness to life-threatening severe dengue characterized by plasma leakage, hemorrhage, and organ failure [1]. Transmitted primarily by *Aedes aegypti* and *Aedes albopictus* mosquitoes, the virus encompasses four antigenically distinct serotypes (DENV-1 through DENV-4), each capable of inducing both primary infection and, upon subsequent exposure to a heterologous serotype, a more severe immunopathological response [2]. Globally, dengue continues to expand geographically, placing nearly half of the world’s population at risk. The World Health Organization (WHO) estimates approximately 390 million dengue infections annually, of which roughly 96 million manifests clinically (WHO fact sheet, Dengue August 2025, https://www.who.int/news-room/fact-sheets/detail/dengue-and-severe-dengue). Over the past two decades, reported case counts have increased eight-fold, driven by urbanization, increased international travel, climate change, and inadequate vector control measures. Dengue is now endemic in more than 100 countries across tropical and subtropical regions of the Americas, South-East Asia, the Western Pacific, Africa, and the Eastern Mediterranean.

Early identification of patients at risk of severe disease remains one of the most pressing challenges in dengue clinical management [3, 4]. The clinical course of dengue is characteristically triphasic, encompassing a febrile phase (days 1–3), a critical phase (days 4–6) during which plasma leakage may precipitate dengue shock syndrome, and a recovery phase. The overlap of clinical features across severity strata particularly during the early febrile phase renders timely risk stratification both critical and elusive.

Despite the 2009 WHO dengue classification system, which introduced “warning signs” as clinical predictors of severe dengue, evidence regarding their individual and combined predictive value remains inconsistent [3, 5]. Laboratory markers such as leukopenia, thrombocytopenia, and elevated hematocrit are routinely monitored; however, their sensitivity and specificity for predicting progression to severe dengue are suboptimal when assessed in isolation. Biomarkers including NS1 antigen levels, inflammatory cytokines, and endothelial permeability indices have shown promise in exploratory studies but have yet to be validated prospectively in diverse clinical settings [3, 6].

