### Study cohorts

Blood samples from patients are collected as per the WHO revised 2009 case classification [1] as: (1) dengue without warning signs (DwoWS), (2) dengue with warning signs (DWS) and (3) severe dengue (SD). Additionally, non-dengue samples will be collected from DENV-negative healthy controls (HCs). 100 individuals from each category will be collected in Guatemala and will serve as the discovery cohort, while 150 individuals from each category will be collected from India and serve as the validation cohort. The patient inclusion and exclusion criteria are presented in Table 1. Additional cohorts from Guatemala, Brazil and Honduras will be used for further validation of the dengue severity biomarkers. Validation of any additional cohorts requires a local ethical clearance, as well as approval from both the Swedish Ethical Review Authority and the COMBAT General Assembly.

**Table 1 Tab1:** Inclusion and Exclusion Criteria for patient enrolment

Inclusion Criteria: The criteria for enrolling the patients in the respective groups.
**Group 1**: Dengue without warning signs (DwoWS) Patients presenting with the following symptoms and confirmed positive for dengue infection following anti-dengue IgM or NS1 ELISA (Enzyme-linked Immunosorbent Assay) lab tests. Symptoms are fever along with at least two of the following: • Myalgia, arthralgia • Nausea and/or vomiting • Rashes • Leukopenia
**Group 2**: DENV with warning signs (DWS) Patients with the above symptoms and any of the following clinical signs: • Abdominal pain with tenderness • Persistent vomiting • Fluid accumulation • Mucosal bleeding • Restlessness, lethargy • Liver enlargement >2 cm • Laboratory findings: An increase in hematocrit levels and a rapid decrease in platelet count
**Group 3**: Severe dengue (SD) Patients with: • Severe plasma leakage leading to hypovolemic shock (dengue shock syndrome) and fluid accumulation with respiratory distress • Severe bleeding, such as epistaxis, and internal bleeding, evaluated by a clinician • Severe organ involvement with any of the following symptoms: - Liver AST or ALT ≥ 1000 - CNS: impaired consciousness - Heart and other organs failure
**Exclusion criteria**: Individuals with the following characteristics were not enrolled.

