#### Development of dengue severity Flex panel

As the main objective of the dengue severity panel is clinical deployment, we will develop a focused proteomics panel of 5–10 biomarkers derived from the mechanism-informed biomarker discovery that follows our integrative omics analysis of severe dengue. Discovery will be performed using the Olink^®^ Reveal platform, which profiles 1034 proteins, and the resulting candidates will be carried forward into a targeted Olink^®^ Flex assay containing the 5–10 prioritized biomarkers. The panel will be validated in both the Guatemala and India cohorts, with subsequent validation in additional independent cohorts.

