### Study endpoint

#### Primary endpoints

Multi-omic (transcriptomic, proteomic, metabolomic and glycomic) signatures that differ significantly across dengue severity categories.A validated multi-omics-derived host biomarker panel that predicts progression to severe dengue.

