#### Secondary endpoints

Dysregulated immune and metabolic pathways associated with disease severity, identified through integrative multi-omic analysis.Reproducibility of candidate biomarkers and pathways in the independent India (validation) cohort and additional external cohorts.Discrimination and calibration performance of machine-learning models integrating clinical, laboratory, demographic, virological and multi-omics features for severity prediction.Analytical and clinical performance of the focused 5–10 biomarker Olink^®^ Flex dengue severity panel.Associations between DENV serotype, host immunometabolic profile and disease severity.

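### No bedside reference model is stated for the biomarker panel or the AI models, so the analyses as written would not show whether the panel adds to routine clinical and laboratory information

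*Protocol article*

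**What the plan says.** The Background gives the motivation. Warning signs have inconsistent predictive value, and of routine laboratory markers it says that "their sensitivity and specificity for predicting progression to severe dengue are suboptimal when assessed in isolation". The Flex panel section names clinical deployment as the panel's purpose.

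The evaluation is set out in four places:

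- **AI models section, comparison.** Logistic regression, random forests, XGBoost, support vector machines and neural networks "will be trained and systematically compared for DENV severity prediction". On inputs: "The models will integrate available clinical, laboratory, demographic, virological, and multi-omics data".
- **AI models section, measures.** "Model performance will be assessed using AUROC, AUPRC, sensitivity, specificity, F1-score, calibration, and decision-curve analysis". SHAP and LIME are planned for interpretability.
- **Flex panel section.** "The panel will be validated in both the Guatemala and India cohorts", followed by further independent cohorts. No comparator is named.
- **Endpoints.** One primary endpoint is "A validated multi-omics-derived host biomarker panel that predicts progression to severe dengue". One secondary endpoint is "Analytical and clinical performance of the focused 5–10 biomarker Olink" Flex panel; another is the discrimination and calibration of the integrated models. All are stand-alone.

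Table 1 defines the severity groups partly by routine findings. For dengue with warning signs these include "An increase in hematocrit levels and a rapid decrease in platelet count", abdominal pain and persistent vomiting. For severe dengue they include AST or ALT of at least 1000.

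**The concern.** The argument for the study is that bedside predictors are not good enough. Support for a new panel then needs an estimate of what it adds to them. The plan compares algorithms with one another and reports the panel's performance alone, so that quantity is never stated as a target.

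The integrated models are the harder ones to read. Their inputs include variables that help assign the outcome label. The Study cohorts section also allows the predictor sample to be taken at the point of deterioration, when those values may already be abnormal. High discrimination could then come from platelets, hematocrit and transaminases, with little from the omics. SHAP and LIME apportion predictions within one fitted model; they do not estimate how well a model without the omics would do. Decision-curve analysis could carry the comparison, but no bedside strategy is named for it.

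At stake is the deployment case for the panel: a good result could not be told apart from a restatement of routine tests.

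**Working it through.** **1. The plan's own sample-size figure.** The Statistical analysis section gives 67 per group for RNA-seq (20,000 genes, 100 prognostic, mean count 5, dispersion 0.5, fold change 2, power 0.8, FDR 0.01).

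- Per-gene alpha = (0.8 × 100 × 0.01) / (19,900 × 0.99) = 4.06 × 10⁻⁵.
- Exact-test power is 0.793 at n = 66 and 0.804 at n = 67, so 67 reproduces.
- 67 / 0.70 = 95.7, so 96, which the plan rounds up to 100.

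The figure is sound, but it concerns gene-level differences and says nothing about comparing predictions.

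**2. Is a reference model or added-value analysis stated?**

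| Place | What is compared | Bedside reference |
|---|---|---|
| AI models section | Algorithms with each other, on pooled inputs | None named |
| Flex panel section | Nothing; validation only | None named |
| Primary endpoint (panel) | Nothing; stand-alone prediction | None named |
| Secondary endpoints | Nothing; stand-alone performance | None named |

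**3. Are the reference variables available?** Table 2 lists age, sex, days since symptom onset, platelets, hematocrit, AST, ALT, abdominal pain and nausea/vomiting. It does not list mucosal bleeding, restlessness or lethargy, liver enlargement or fluid accumulation. Those appear only as classification criteria in Table 1.

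**4. How precise would the comparison be?** From the protocol: 150 per group in India and 30% loss, giving 150 × 0.7 = 105 severe and 2 × 105 = 210 non-severe dengue patients. Assumed, because the protocol gives no values: AUROC A = 0.80 for both models, and correlation r = 0.3 to 0.7 between the two AUROC estimates.

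Hanley–McNeil: SE² = [A(1−A) + (n₁−1)(Q₁−A²) + (n₀−1)(Q₂−A²)] / (n₁n₀), with Q₁ = A/(2−A) = 0.6667 and Q₂ = 2A²/(1+A) = 0.7111.

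- 105 vs 210: (0.16 + 104 × 0.0267 + 209 × 0.0711) / 22,050 = 0.000807, so SE = 0.028.
- Half-width = 1.96 × √(2 × SE² × (1−r)) = 0.066, 0.056 and 0.043 for r = 0.3, 0.5 and 0.7.
- If only 30 severe patients were sampled before becoming severe (an assumed number): SE = 0.050, and half-widths are 0.116, 0.098 and 0.076.

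The Statistical analysis section also describes 150 as the size retained after loss. On that reading, 150 vs 300 gives SE = 0.024 and half-widths of 0.055 to 0.036.

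**5. Power of a paired AUROC comparison** (two-sided 5%, r = 0.3 to 0.5, AUROC values assumed):

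| India | 0.70 vs 0.80 | 0.75 vs 0.80 |
|---|---|---|
| 150 vs 300 | 91–97% | 40–52% |
| 105 vs 210 | 79–90% | 30–39% |

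A gain near 0.10 is testable; one near 0.05 would be estimated imprecisely.

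**The case against.** The strongest reply is that this is a condensed article. A reference model and an added-value measure are often left to an analysis plan, which is not shown here. Nothing in the quoted sentences is false. The Background also defines the gap as the lack of a tool integrating bedside, laboratory and biomarker data, which the AI models do address. The triage benefit is worded conditionally, as something the findings may inform.

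Much of this stands, and it limits the point. A reader might infer that the study cannot show added value. The documents do not support that: most of the data are collected, and a clinical-only model could be fitted without changing the design. A reader might infer that the panel is compared with the AI models; in fact it has no stated comparator. Nor is AUROC the only measure, since decision-curve analysis is planned. And one cannot assume that every warning sign is recorded at sampling, because Table 2 does not list them all.

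What does not stand is the appeal to condensation. The article specifies its model families, validation schemes, performance measures and endpoints. Those endpoints fix stand-alone performance as the thing to be reported. Showing that biomarkers belong in an integrated tool still requires the same tool without them.

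**Conclusion.** The concern holds in a limited form. As written, the planned analyses would leave the added value of the panel over routine bedside and laboratory information unestimated, and a high AUROC for an integrated model could not be credited to the omics. The omics discovery aims and the RNA-seq sample size are unaffected.

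The comparison would be informative at the planned size. Its half-width is about 0.04 to 0.07 with 105 vs 210, and about 0.08 to 0.12 if only 30 severe patients were sampled early. These figures rest on an assumed AUROC of 0.80 and assumed correlations of 0.3 to 0.7; the 30 is also an assumption. The documents do not support reading this as proof that the unseen analysis plan lacks such an analysis, or as a claim that the panel has no added value.

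**What to change.** In the AI models section and the secondary endpoints:

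1. **Add a reference model**: age, sex, day of illness, platelets, hematocrit, AST/ALT and the warning-sign items recorded at the predictor sample. Train it in Guatemala and lock it before the India data are analysed.
2. **Report in India**, for severe versus non-severe dengue, the paired AUROC difference with 95% CI between reference plus panel and reference alone, with the panel-alone result beside it. This outcome avoids the circularity of warning signs defining the middle group.
3. **Make the main comparison among participants who do not yet meet severe-dengue criteria at the predictor sample.** Otherwise AST/ALT is partly circular for severe dengue and would favour the reference.
4. **Report any net-benefit difference after reweighting to a stated prevalence of severe dengue**, because the groups are filled by quota.
5. **Warning signs missing from Table 2**: take them from the classification record or add them as fields in India. An item can enter the locked model only if it can also be recovered for Guatemala, where 170 participants were already enrolled by June 2026. Failing that, use only the listed items and say so.

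I would report the estimate and its interval without a pass/fail rule, given 30–39% power for a gain of 0.05 at 105 vs 210.

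The cost is one extra model, possibly a few form fields, and endpoint wording. The headline figure will be less favourable and less precise, especially in the subset sampled before severity.

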• Patients below the age of 18 years • Pregnant, immunocompromised or undergoing chemotherapy, on steroids or immunosuppressive drugs in the last year or with liver cirrhosis • Co-infection with a non-dengue pathogen • Cases with a lab-confirmed dengue infection within the past three months

The study is designed to investigate the progression of dengue infection in patients, from without warning signs, to with warning signs to severe dengue, which varies between cases. If a patient recruited in the category “DwoWS” develops symptoms correlating with severity and receives intensive care, they will then be re-categorized into the second “DWS” or third “SD” group. Keeping in mind the complexity of dengue presentation, subcategorization of the patients will be performed as necessary to establish the degree of severity depending on the timepoint of recruitment and the points of sample collection. The highest (peak) severity category reached during the acute illness constitutes the participant’s definitive severity classification and serves as the primary outcome label for all biomarker analyses. For incorporation into the biomarker discovery and validation analyses, the earliest sample for each participant collected before or at the point of clinical deterioration is used as the predictor, and the definitive peak severity category is used as the outcome.

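### Some clinical and laboratory inputs to the severity models also define the severity label, so discrimination is inflated for participants who already meet the criterion at sampling

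*Protocol article*

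**What the plan says.** All references are to the protocol article.

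- **Outcome.** In Study cohorts, the highest category reached during the acute illness "constitutes the participant’s definitive severity classification and serves as the primary outcome label for all biomarker analyses". Table 1 sets the categories. Among the items for dengue with warning signs (DWS) are abdominal pain with tenderness, persistent vomiting and "Laboratory findings: An increase in hematocrit levels and a rapid decrease in platelet count". Among the items for SD is "Liver AST or ALT ≥ 1000".
- **Predictor sample.** The same section states that "the earliest sample for each participant collected before or at the point of clinical deterioration is used as the predictor". Under Study procedures, the first inpatient sample falls within the first two days of hospitalization.
- **Data recorded.** Table 2 lists abdominal pain and nausea/vomiting as present or absent at sampling. It also lists platelets, hematocrit, AST and ALT.
- **Model inputs.** The AI section says "The models will integrate available clinical, laboratory, demographic, virological, and multi-omics data", with feature selection and dimension reduction. It does not set aside the items that define the label.
- **Endpoint.** A secondary endpoint is "Discrimination and calibration performance of machine-learning models integrating clinical, laboratory, demographic, virological and multi-omics features for severity prediction".

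**The concern.** A predictor that is also part of the outcome definition can separate the groups without saying anything about who will deteriorate. The article fixes both sides, the label in Study cohorts and the input set in the AI section and the secondary endpoints, and the two share items. For a participant whose qualifying value is already present in the predictor sample, the model reads the label back from the input.

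Two things would be at stake. First, AUROC, sensitivity and specificity of the integrated models would overstate prognostic value. The planned safeguards would not show this: feature selection tends to keep an item that separates the groups well, and external or leave-one-site-out validation applies the same case definition everywhere, so the excess recurs at each site and can look like generalizability. Second, it would become harder to see what omics adds to bedside data. A clinical block that partly contains the label can hide a real omics gain, and a combined model can look accurate with little omics contribution.

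**Working it through.** **Plan's own figure.** The article states no AUROC or other expected model performance, so there is none to reproduce. Its one derived figure, 67 subjects per group for RNA-seq, plays no part here.

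**Step 1: compare the label items (Table 1) with the inputs (Table 2).**

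| Label item | Input recorded | Match |
|---|---|---|
| SD: AST or ALT at or above 1000 | AST, ALT values | Exact |
| DWS: abdominal pain with tenderness | Abdominal pain, yes/no | Partial: tenderness not recorded |
| DWS: persistent vomiting | Nausea/vomiting, yes/no | Partial: nausea or vomiting is also a Group 1 entry symptom |
| DWS: hematocrit rise with rapid platelet fall | Single hematocrit and platelet values | Partial: one value is not a change |
| DWS: mucosal bleeding, fluid accumulation, liver enlargement | Not in Table 2 | None |
| SD: shock, impaired consciousness | Not in Table 2 | None |

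**Step 2: can the criterion already be met at the predictor sample?** Yes, by three routes. The timing rule admits a sample taken at deterioration as well as before it. Table 1 lets patients enter directly as DWS or SD. The first inpatient sample may come up to two days into the stay.

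**Step 3: size for an exactly matching item.** Let g be the share of SD cases whose predictor sample already meets the AST/ALT criterion. No participant with a lower peak category can meet it, because meeting it would make the participant SD. Let A be the AUROC for the remaining SD cases against non-cases, which is the prognostic quantity wanted. A model that uses the item ranks the share g above every non-case, so

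reported AUROC = g × 1 + (1 − g) × A.

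The documents give neither g nor A; both are assumed.

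| A | g = 0.1 | g = 0.3 | g = 0.5 |
|---|---|---|---|
| 0.50 | 0.55 | 0.65 | 0.75 |
| 0.70 | 0.73 | 0.79 | 0.85 |
| 0.80 | 0.82 | 0.86 | 0.90 |

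Example: 0.3 + 0.7 × 0.70 = 0.79. A simulation with A = 0.70 gave 0.730, 0.790 and 0.850 at the three values of g, in agreement. At g = 0 the excess disappears.

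**Step 4: partly matching items.** A yes/no item present in a share f of DWS patients and a share p of patients without warning signs has AUROC 0.5 + (f − p)/2. For f = 0.5 (assumed), this is 0.75 at p = 0 but 0.65 at p = 0.2 (assumed). Since p is above zero for inputs such as nausea/vomiting, the inflation is smaller than an exact match would give.

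**The case against.** The strongest reply is that the overlap is narrow and depends on timing. Only AST/ALT matches a label item exactly. In a patient sampled before deterioration, all these variables are legitimate baseline predictors, and the article does have a timing rule. The study's rationale is a tool that combines bedside features, routine laboratory values and biomarkers, so stripping out routine data would work against it. Final predictor lists are commonly left to an analysis plan, and only one of five secondary endpoints is involved.

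Much of this stands, and it rules out stronger readings that a reader might infer:

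- *The DWS label is a deterministic function of the inputs, so one warning sign alone yields an AUROC of 0.65, 0.75 or 0.85 (f = 0.3, 0.5, 0.7).* This needs p = 0, and Table 1 contradicts that for vomiting. The hematocrit and platelet sign is a change that one sample does not determine.
- *Troponin, NT-proBNP and creatinine are label items too.* Table 1 names heart and other organ failure but gives no laboratory threshold for it.
- *The problem exists whatever the sampling time.* It arises only where the criterion is already met at the predictor sample.

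The reply does not remove the core. The timing rule itself lets in samples taken at deterioration. Nor is this only detail left for later: an analysis plan that followed the stated label, timing rule and inputs would carry the overlap into the reported performance.

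**Conclusion.** The point holds in a limited form. As written, the integrated models may use inputs that partly restate their outcome for participants who already meet the category at sampling. The overlap is exact for AST/ALT and SD, and partial for abdominal pain, nausea/vomiting, hematocrit and platelets and DWS. Reported discrimination is inflated to the extent that such participants are included, and validation under the same case definition does not reveal it.

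The size cannot be fixed from the documents. With g assumed at 0.1 to 0.3 and a true AUROC of 0.70, the excess is 0.03 to 0.09. This rests on the model making full use of the AST/ALT threshold and on no non-case meeting it. The excess from the DWS items is smaller than an exact match would give, but is not quantified. The article also does not specify a binary DWS model, although its three-level label permits one.

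The primary omics signatures and the protein-only Flex panel do not take these inputs and are not directly affected.

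**What to change.** Add to the AI section, before any model is trained:

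1. For each outcome contrast, primary performance of the integrated models is estimated in one of two ways, named in advance. (a) Only in participants who did not yet meet that category's criteria at the predictor sample, keeping all clinical and laboratory inputs, including warning signs as predictors of later SD. (b) With the items that define that contrast removed from the inputs.
2. Participants who already meet the category at the predictor sample are reported separately.
3. Omics-only, clinical-only and combined models are reported on the same participants, so that the omics increment is visible.

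Option (a) keeps the bedside data that the rationale calls for and answers the question of progression directly. It requires the category at the predictor sample to be known; the article already foresees subcategorizing patients by time of recruitment and of sample collection.

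**Cost.** Analysis wording and a few extra model runs, with no new recruitment. Option (a) loses participants who met any criterion of the category at sampling, not only the AST/ALT one. For illustration, if half of SD cases did, the planned 100 in Guatemala and 150 in India would fall to 50 and 75. Option (b) keeps the numbers but gives up some routine predictors. Under either option the reported AUROC is likely to be somewhat lower.

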### Study design

COMBAT is a prospective, multicenter, observational longitudinal study designed to characterize host responses to dengue infection without altering standard clinical management.

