### Study procedures

A single blood sample is collected from the non-hospitalized patients, while two blood samples per participant are collected from the hospitalized patients. The first one is taken within the first two days of hospitalization, and the second at discharge. A questionnaire is administered at the time of blood collection (Table 2). Total participation time is less than 15 min. For Guatemala, whole blood is collected in Tempus™ tube for transcriptomics and in Cytodelics medium for flow cytometry, while plasma from EDTA blood and serum are collected for proteomics, metabolomics and glycomics. For India, whole blood (3 ml) is collected in Tempus™ tubes for transcriptomics and 7–8 ml in BD Vacutainer CPT™ Cell Preparation Tubes for plasma separation and PBMC isolation.

**Table 2 Tab2:** Routine clinical investigations performed in dengue cases in all the cohorts

Parameters	Unit of Measurement
Age	In years
Sex	Male/Female

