**Disease symptoms at the time of sampling**	
Duration of symptoms onset at sample collection	In days
Duration of hospitalization at sample collection	In days
Fever	Yes/No
Body pain	Yes/No
Joint pain (arthralgia)	Yes/No
Rash	Yes/No
Nausea/vomiting	Yes/No
Night sweats	Yes/No
Retro-orbital pain	Yes/No
Abdominal pain	Yes/No
Headache	Yes/No
Chills/ rigor	Yes/No
Burning micturition	Yes/No
Dizziness	Yes/No

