**Clinical biochemistry**	
Hemoglobin	g/dL
White Blood Cells	(value)/µL
Differential Lymphocyte Count (eosinophils, neutrophils, lymphocytes)	(value)/ µL
Platelets	(value)/ µL
Hematocrit	%
Procalcitonin	mcg/L
Total bilirubin	mg/dL
Aspartate Transaminase	IU/L
Alanine Transaminase	IU/L
Alkaline Phosphatase	U/L
Urea	mg/dL
Creatinine	mg/dL
Partial Thromboplastin Time	seconds
Activated Partial Thromboplastin Time	seconds
Serum Lactate Dehydrogenase	U/L
Lactate Oxidase (Arterial Blood Gas)	mg/dL
Creatinine Phosphokinase	U/L
Troponin T	ng/mL
N-Terminal Pro- B-Type Natriuretic Protein	pg/mL

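### The severity models accept all available clinical data, including days in hospital at sampling, so they can partly predict severity from care already given

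*Protocol article*

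**What the plan says.** The section on artificial intelligence models sets the inputs by data class and by availability: "The models will integrate available clinical, laboratory, demographic, virological, and multi-omics data, using feature-selection and dimensionality-reduction approaches". It names no variable to be left out.

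Table 2 lists the recorded variables. Under symptoms at sampling it has "Duration of hospitalization at sample collection", in days. Under clinical biochemistry it has organ-injury and blood-gas items, among them troponin T, "N-Terminal Pro- B-Type Natriuretic Protein" and an arterial blood gas lactate entry. The table is titled "Routine clinical investigations performed in dengue cases in all the cohorts".

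Study procedures ties sampling to care setting: "A single blood sample is collected from the non-hospitalized patients, while two blood samples per participant are collected from the hospitalized patients". For inpatients, "The first one is taken within the first two days of hospitalization, and the second at discharge". Under Study design, the study is "designed to characterize host responses to dengue infection without altering standard clinical management".

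The text after Table 1 makes peak severity the outcome and takes as predictor the earliest sample before or at deterioration. It also mentions receipt of intensive care in the rule that moves a patient out of the no-warning-signs group. Discrimination and calibration of the models are a secondary endpoint.

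**The concern.** Hospital days at sampling describe where the patient was being treated. They are not a measurement of host response. An outpatient has none, and an inpatient's first sample already follows admission. Since sicker patients are more likely to be admitted, the variable carries the clinician's own assessment of severity into a model meant to predict severity.

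The Background names avoidable admissions and premature discharge as the decisions that need better tools, and the Abstract claims improved triage. A model that reads admission status cannot inform the decision to admit, and its AUROC cannot be credited to host biology. Selecting features on their association with the outcome would tend to keep such a variable.

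A second, conditional route exists. If the organ-injury or blood-gas tests turn out to be done more often in sicker patients, whether a value is present would carry the same information. The article does not document this, and the title of Table 2 argues against it.

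**Working it through.** The plan gives no figure on this point, so there is none to reproduce. The check asks what a care variable could contribute on its own.

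**Inputs.** From the protocol: three dengue groups of equal size (100 each in Guatemala, 150 each in India), with peak severity as the outcome. Assumed, because the documents give no rates: the share of each group in hospital at the sample used as predictor.

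**Formula.** For a yes/no flag, with the two milder groups equal in size, the AUROC for severe dengue (SD) against dengue without (DwoWS) and with (DWS) warning signs is

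AUROC = 0.5 + [p(SD) − (p(DwoWS) + p(DWS))/2] / 2.

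| Assumed % in hospital, DwoWS/DWS/SD | Calculation | AUROC for SD |
|---|---|---|
| 0/50/100 | 0.5 + (1.00 − 0.25)/2 | 0.875 |
| 10/50/95 | 0.5 + (0.95 − 0.30)/2 | 0.825 |
| 10/80/100 | 0.5 + (1.00 − 0.45)/2 | 0.775 |
| 20/80/100 | 0.5 + (1.00 − 0.50)/2 | 0.75 |
| 50/90/100 | 0.5 + (1.00 − 0.70)/2 | 0.65 |
| 90/100/100 | 0.5 + (1.00 − 0.95)/2 | 0.525 |
| 100/100/100 | 0.5 + (1.00 − 1.00)/2 | 0.50 |

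At 10/80/100%, the same flag separates DwoWS from the other two groups with AUROC 0.5 + (0.90 − 0.10)/2 = 0.90.

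Two features would lower these values. A patient who later becomes severe but whose earliest sample was taken as an outpatient counts as not in hospital; each 10 points off p(SD) takes 0.10/2 = 0.05 off the AUROC. And if outpatients are coded zero, inpatients sampled on the day of admission may look the same.

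**Does external validation expose it?** A ridge logistic model using four care flags and no biology was simulated 300 times, with 100 per group for training and 150 per group for validation. Training rates (DwoWS/DWS/SD) were 10/50/95% for one flag, 5/30/80% for two and 10/30/70% for the fourth, independent within each group. The training AUROC was 0.96. The external AUROC depended on the validation sites:

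- same care pattern: 0.96;
- weaker pattern (50/75/97% for the first flag, 20/30/50% for the others): 0.80;
- no link between care and severity: 0.50.

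Three of the four flags stand for selective testing, which is not documented, and tests ordered together would not be independent. These values therefore show the mechanism and do not estimate its size in this study.

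**Do the stated safeguards remove it?** The earliest-sample rule chooses which sample is used, not which variables; it also allows a sample at deterioration, and an inpatient's first sample may be up to two days into the stay. SHAP and LIME would probably show a dominant hospital variable, but the article does not say what follows if they do.

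**The case against.** The strongest reply is that an article need not print a predictor list. Hospital days are not named as a model input; they stand beside days since symptom onset as a description of sampling time. The word available may only reflect that the platforms differ by country, with metabolomics planned for Guatemala and RNA-seq and Olink for India. The detailed list and the handling of missing values may sit in an analysis plan that is not shown.

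Much of this stands, and the lack of a list or an imputation rule is not the point here. The point is the inclusion rule that the article does state: hospital days satisfy it on either reading of the word, and nothing takes them out.

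Three stronger readings are tempting and are not supported.

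- A reader might infer that troponin, natriuretic peptide or blood gases are ordered only in sick patients. No section says so, and the title of Table 2 says the reverse. Leaving standard management unaltered does not itself mean that testing depends on severity. The participation time of under 15 minutes covers all participants and says nothing about which tests are run.
- A reader might infer that external validation cannot reveal the problem. It can where care patterns differ, as the 0.80 and 0.50 results show, and the limitations paragraph says diagnostic capacity varies across sites.
- A reader might infer that the biomarker panel is compromised. The primary endpoints concern omics signatures and an omics-derived panel, and the Flex assay contains 5–10 proteins. Neither is shown to use Table 2 variables.

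**Conclusion.** The concern holds in a limited form. As written, the input rule admits a variable that distinguishes inpatients from outpatients by construction, and no stated safeguard excludes it. Leakage through selectively ordered tests is only a possibility to be checked against the data.

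The size cannot be fixed from the article. Under the assumed rates, a single care flag gives an AUROC for severe dengue from 0.50 to about 0.88. The low end applies if nearly all dengue participants are in hospital when sampled. These figures describe the flag alone; they do not say how far a model that also holds omics and real laboratory values would be inflated.

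Only the machine-learning secondary endpoint is touched. The point should be fixed because the change is nearly free and the AUROC is hard to interpret for triage without it. It does not put the study's main conclusions at risk.

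**What to change.** In the section on artificial intelligence models, make these changes:

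1. Exclude duration of hospitalization, and any other record of care setting or care given, from the inputs of the reported severity models. It can stay in the dataset as a descriptor.
2. Keep demographics, day of illness, symptoms, virology, omics, and laboratory items measured at the draw regardless of severity.
3. Tabulate the completeness of each laboratory item by severity group and country. Leave out of the primary model any item whose availability differs materially by severity, and allow no missingness indicators or native missing-value splits for such items.
4. Optionally, report a model built on missingness alone as a negative control; its AUROC should be near 0.50.

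The cost is one paragraph and one table, with fewer inputs and possibly a lower reported AUROC. Recruitment in India is stated to start only in July 2026, so the rule is best fixed before the validation data are analysed.
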